## Abstract

**Background:**

Posttraumatic Stress Disorder (PTSD) is a serious mental health condition with substantial costs to individuals and society. Among military veterans, the lifetime prevalence of PTSD has been estimated to be as high as 20%. Numerous research studies have demonstrated that short-term cognitive-behavioral psychotherapies, such as Cognitive Processing Therapy (CPT), lead to substantial and sustained improvements in PTSD symptoms. Despite known benefits, only a minority of clinicians provide these therapies. Transferring this research knowledge into clinical settings remains one of the largest hurdles to improving the health of veterans with PTSD. Attending a workshop alone is insufficient to promote adequate knowledge transfer and sustained skill; however, relatively little research has been conducted to identify effective post-training support strategies.

**Methods:**

The current study investigates whether clinicians receiving post-workshop support (six-month duration) will deliver CPT with greater fidelity (*i.e*., psychotherapy adherence and competence) and have improved patient outcomes compared with clinicians receiving no formal post-workshop support. The study conditions are: technology-enhanced group tele-consultation; standard group tele-consultation; and fidelity assessment with no consultation. The primary outcome is independent assessment (via audio-recordings) of the clinicians’ adherence and competence in delivering CPT. The secondary outcome is observed changes in patient symptoms during and following treatment as a function of clinician fidelity. Post-consultation interviews with clinicians will help identify facilitators and barriers to psychotherapy skill acquisition. The study results will inform how best to implement and transfer evidence-based psychotherapy (*e.g*., CPT) to clinical settings to attain comparable outcomes to those observed in research settings.

**Discussion:**

Findings will deepen our understanding of how much and what type of support is needed following a workshop to help clinicians become proficient in delivering a new protocol. Several influences on clinician learning and patient outcomes will be discussed. An evidence-based model of clinical consultation will be developed, with the ultimate goal of informing policy and influencing best practice in clinical consultation.

**Trial registration:**

ClinicalTrials.gov: NCT01861769

## Background

The lifetime prevalence of PTSD is approximately 9% in Canada’s general population [1], 6.8% in the United States (U.S.) [2], and 15% to 19% among veterans of the recent conflicts in Iraq and Afghanistan [3,4]. PTSD is associated with substantial functional impairment, suicide risk [5], numerous physical diseases [6-9], higher rates of mortality, high healthcare utilization and costs, and annual productivity loss of over $3 billion in the U.S. [10-15]. Studies of chronic PTSD indicate little change over time without active intervention [16].

Cognitive-behavioral therapies (CBT) for PTSD have been shown to be efficacious and are recommended as first-line therapies in treatment guidelines [17,18]. Cognitive Processing Therapy (CPT) is a 12-session, trauma-focused cognitive therapy that targets symptoms of PTSD and its comorbidities [19] that results in sustained, significant reductions in symptoms and increases in quality of life for diverse populations [20-34]. Despite substantial efficacy data, clinicians do not routinely deliver CPT or other evidence-based psychotherapies (EBPs) [35].

In Canada, the U.S., and the United Kingdom, policymakers have prioritized investigating the implementation of EBPs to address this critical gap between research and practice [36]. In response to the shortage of adequately trained clinicians [37], policymakers have issued mandates, provided incentives, and invested billions of dollars in EBP training of clinicians in public mental health settings [35,38]. However, many of the utilized training strategies are not empirically supported, and much remains to be learned about how best to disseminate and implement EBPs in routine clinical practice. Without proven strategies to increase clinician use, there is little assurance that the investment that individuals and organizations make to develop EBPs will ultimately benefit patients. Both the Canadian Institute of Health Research (CIHR)’s Health Research Roadmap (2009 to 2014; [39]) and the U.S. National Institute of Mental Health [40] note the growing need for implementation science to better understand the determinants and uptake of knowledge. The use of evidence-based implementation strategies will ensure that money spent on treatment research has maximum impact.

Didactic workshops are a cornerstone of existing large-scale EBP implementation efforts [35,38,41]. However, workshops alone are insufficient to promote high-quality implementation and sustainment of EBPs in clinical settings. After a single workshop, most clinicians are unable to deliver EBPs with fidelity (adherence to the protocol and competence in delivery of the interventions [42,43]). Fidelity to EBPs has been shown to predict patient outcomes for a number of mental health disorders [44-49], and has been associated with PTSD symptom outcomes in our preliminary research on CPT. To adequately prepare clinicians to deliver EBPs with fidelity, training packages that include post-workshop consultation and feedback have emerged as best practices, but little is understood about the relative benefits of different consultation strategies [41,42].

Previous comparisons of post-workshop consultation strategies have lacked external validity (*e.g*., have been conducted under controlled conditions with highly motivated therapists in training clinics), rarely assessed fidelity objectively and in real-world practice conditions [50], had poor follow-up rates, rarely addressed barriers to implementation, and have demonstrated less than optimal results [41-43]. Thus, there is little empirical evidence to identify optimal, cost-efficient consultation and feedback strategies. Feedback based on observation is considered the ‘gold standard’ for training and is assumed to be necessary for optimal fidelity [42]. Without more direct observation of therapist behavior, there is limited opportunity for the expert to provide the type of feedback required to promote fidelity and high-quality service delivery [51]. The one randomized study that tested this assumption found that coaching based on review of session material resulted in greater change talk among clients [52]. This study evaluated individual-level consultation under controlled conditions with limited external validity, and had no comparison to group consultation strategies. Individual feedback and consultation is too costly and resource-intensive to be feasible in large healthcare delivery systems [53]. One strategy used in several training initiatives is expert-delivered group tele-consultation, in which clinicians receive feedback from an expert on their treatment provision based solely on their verbal reports of their sessions [35]. However, the association between clinician report of their behavior and objective assessment of therapy fidelity is unknown.

To address this limitation of the standard consultation strategy, the present study also tests a technology-enhanced group tele-consultation. Our approach involves an expert and group members listening to, and providing feedback on, portions of group members’ audio-recorded therapy sessions on a weekly basis. This strategy provides exposure to a broad sample of case material for vicarious learning, and also allows the expert to provide more specific and accurate feedback than in standard consultation. However, while it provides the opportunity for more in-depth discussion of work samples for the clinicians who present in a given week, the time spent on the audio review may result in less time for other clinicians in the group to discuss their own cases when not presenting audio. Thus, each consultation strategy may have unique advantages over the other. The two consultation conditions will be compared to a no consultation (fidelity monitoring only) condition in order to assess the incremental benefit of post-workshop consultation. The study is funded by the Canadian Institutes of Health Research and represents the collaborative efforts of investigators at Ryerson University, Veterans Affairs Canada’s Operational Stress Injury National Network (OSINN), the U.S. National Center for PTSD, and Boston University. This article describes the study’s aims, method and proposed analytic strategy.

### Research questions and hypotheses

Question 1: The principal research question to be addressed is whether different types of post-workshop support for mental health clinicians have differential effects on clinician fidelity to the CPT protocol.

Hypothesis 1: We hypothesize that the technology-enhanced group tele-consultation condition will evidence the highest levels of fidelity, the standard group tele-consultation condition will evidence intermediate levels of fidelity, and the no consultation condition will evidence the lowest fidelity.

Question 2: Is clinician fidelity to the CPT protocol is related to client outcomes?

Hypothesis 2: We hypothesize that fidelity to the CPT protocol, irrespective of consultation condition, will be positively associated with improved client outcomes.

Question 3: What are contextual barriers or facilitators to the skilled use of CPT in their routine practice?

Hypothesis 3: We hypothesize that organizational contextual variables such as local leadership support, organizational structure, and organizational climate, as well as clinician attitudes toward EBPs will influence the uptake of CPT.

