## Methods

This randomized controlled dismantling trial has independent fidelity rating as the primary outcome and patient outcomes as the secondary outcomes. Clinicians are randomly assigned to six months of post-workshop support following an intensive two-day CPT workshop delivered by the last author. The conditions are: standard group tele-consultation, technology-enhanced group tele-consultation, or no consultation/fidelity monitoring only. The post-workshop consultation conditions vary as to whether audio-recorded therapy sessions and other work samples, such as CPT worksheets, are reviewed in the group. This design permits the evaluation of the additive value of each of the elements (*i.e*., expert consultation, technology-assisted expert consultation). Follow-up assessments of fidelity will be conducted at six months post-workshop for clinicians, and follow-up symptom assessments will be conducted at three months post-treatment for patients.

Participation in the study requires that all clinicians consent at least two clients to have all of their CPT sessions audio-recorded for use in consultation and/or fidelity rating. Four therapy sessions will be randomly selected across the six-month period for fidelity rating, and fidelity to treatment will be assessed by trained graduate students and post-doctoral fidelity assessors. Consistent with recommended clinical practice and research trials, patient outcomes will be assessed pre-treatment, at alternate therapy sessions, and at three months post-treatment. A secure web-based application is used to manage the continuous uploading of encrypted audio-recorded therapy sessions to the study server and to protect the privacy and confidentiality of patients and clinicians. Study-provided digital audio-recorders (USB-equipped) are used to record, store and upload CPT sessions to the secure server for fidelity ratings. Study staff retrieve the randomly-selected audio-recordings and assign them to the CPT fidelity raters, who are blinded to study condition. To check if rater blinding has been achieved, fidelity raters will be asked to guess the study condition for each session they rated. Patient self-report data is collected by the clinicians, who then upload the data directly to the server and clinician CPT activity outside of study-related procedures is also recorded.

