### Clinician monthly CPT activity reporting

During the six-month active study period, all clinicians complete a monthly report via a web-based survey on CPT activity. Questions include: the number of CPT sessions provided over the past month (irrespective of patients’ enrollment in the study); cumulative number of new CPT clients seen; frequency, duration, and satisfaction with consultation over the past month (as applicable); and a rating of clinician confidence in their ability to adhere to adherence to the CPT protocol.

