### Proposed analytic strategy

Trial reporting will follow the CONSORT 2010 statement for reporting randomized controlled trials [69]. Analyses will be preceded by careful examination of the descriptive statistics and distributional form of all variables. The effectiveness of randomization will be evaluated by comparing the different conditions on baseline measures, demographics, and key outcome variables using Chi-squared tests and t-tests. The primary analyses will be conducted using random effects regression modeling. These models provide more flexibility in modeling missing data than general linear models and are appropriate for nested data. ‘Intention-to-train’ principles will be used in the analyses of clinicians who are assigned to a consultation modality but either fail to engage or are unable to fulfill the post-workshop participation requirements (*e.g*., do not attend consultation sessions). Analyses of both the intention-to-train and completer samples will be conducted.

To explore the contribution of organization and clinician-level factors to the outcomes of interest, in addition to random effects regression modeling, we will conduct qualitative analyses on interview data. Qualitative and quantitative data will be integrated to facilitate a fine-grained understanding of processes and characteristics that influence training outcomes. Interviews will be analyzed in line with goals, objectives and key research questions. Using content analysis, we will identify analytical categories to describe and explain our observations. Our work will occur in five stages outlined in Pope, Ziebland, and Mays’ framework approach to qualitative analysis [70]: Familiarization; Identifying a Thematic Framework; Indexing; Charting; and Mapping and Interpretation. In the second stage, codes will be derived deductively by identifying categories at the beginning of the research (*e.g*., elements of the CFIR), and inductively by identifying those that emerge gradually from the data. In subsequent phases, survey data on contextual factors will be examined in conjunction with fidelity scores for the purposes of validation, hypothesis generation, and expansion [71,72] to understand ways in which contextual factors influence fidelity to CPT.

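### Hypothesis 3 is about uptake of CPT, but the only quantitative outcome named for the contextual survey data is fidelity, which cannot by itself test an effect on use

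*Protocol article*

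**What the plan says.** Three parts of the protocol article describe the outcome of the contextual aim, and they do not agree.

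- Research questions and hypotheses: Question 3 asks "What are contextual barriers or facilitators to the skilled use of CPT in their routine practice". Hypothesis 3, its counterpart, says that leadership support, structure, climate and attitudes "will influence the uptake of CPT". Neither term is defined.
- Proposed analytic strategy: after the qualitative stages, "survey data on contextual factors will be examined in conjunction with fidelity scores", with the aim "to understand ways in which contextual factors influence fidelity to CPT". The same paragraph opens more broadly: "To explore the contribution of organization and clinician-level factors to the outcomes of interest, in addition to random effects regression modeling", interview data will be analysed qualitatively. The outcomes of interest are not listed.
- Methods: fidelity comes from uploaded sessions. "Study staff retrieve the randomly-selected audio-recordings and assign them to the CPT fidelity raters".

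Two other sources bear on use of CPT. Under Clinician monthly CPT activity reporting, every clinician reports each month for six months "the number of CPT sessions provided over the past month", whether or not the patients are enrolled, and the cumulative number of new CPT clients. Under the section on barriers and facilitators, clinicians are interviewed at baseline, after consultation and three months later, including on barriers to using CPT. The article does not connect the monthly counts to any hypothesis or to the contextual measures.

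**The concern.** Uptake, skilled use and fidelity are different quantities. A clinician in an unsupportive clinic may deliver CPT well but to few patients, or may not deliver it at all. In the first case the fidelity score says nothing about how little CPT was used. In the second there is no fidelity score.

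The stake is interpretation. The Discussion presents the study of training in its organizational context as the first innovation of the project. If context turned out to be unrelated to fidelity, that result could be reported as context not affecting uptake, although no quantitative analysis named in the article had used an uptake measure. The trial already holds a more direct measure, with zero as a valid value, and does not assign it to the hypothesis that it fits.

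**Working it through.** The article gives no figure for Hypothesis 3, so there is nothing to reproduce. The main check sets the statements side by side.

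1. Outcome in the hypothesis: uptake. Outcome in the question: skilled use. Outcome in the analysis: fidelity. Only the last two can be matched without a further definition.
2. Who has the outcome. Fidelity needs a delivered, recorded and uploaded session. The analysis section itself foresees clinicians who do not engage or cannot meet the participation requirements. The monthly counts need only a returned report.
3. How many lack a score. Trial status says that uploading was high but gives no number, so the extent of selection cannot be computed from the document.

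Two simulations show what may follow. **All inputs are assumed; none comes from the article.**

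*Illustration A: the wrong quantity.* Let context C be standard normal, let the tendency to use CPT be U = 0.5·C + √0.75·e, and let fidelity be unrelated to C. Clinicians with the lowest U have no recording.

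| Share without a score | Correlation of C with use (yes/no) | Correlation of C with fidelity among those scored |
|---|---|---|
| 10% | 0.29 | 0.00 |
| 20% | 0.35 | 0.00 |
| 30% | 0.38 | 0.00 |

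A real effect on use is invisible to a fidelity-only analysis. This holds by construction, and it follows from the choice of outcome rather than from the amount of missing data.

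*Illustration B: selection when fidelity is the target.* Let the tendency to deliver be b·C + 0.6·E + noise, with E an unmeasured engagement variable, and let fidelity be 0.2·C + 0.5·E + 0.8·noise. The true slope of fidelity on context is 0.20.

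| Share without a score | Slope, b = 0.5 | Slope, b = 0.8 |
|---|---|---|
| 5% | 0.18 | 0.175 |
| 10% | 0.17 | 0.16 |
| 20% | 0.158 | 0.142 |

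At 20% the shortfall is 1 − 0.158/0.20 = 21% and 1 − 0.142/0.20 = 29%. For scale, 90 clinicians less 20% leaves 72. The residual SD is √(0.5² + 0.8²) = 0.94, so the standard error of the slope is about 0.94/√72 = 0.11. The bias of 0.04 to 0.06 is about half of one standard error. In this model selection is the smaller problem, and the outcome mismatch is the larger one.

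**The case against.** A reader might infer that barriers to using CPT drop out of the study, or that Hypothesis 3 is tested on a wrong outcome and a strong barrier will look like nothing. The document does not support either reading.

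- The interviews are not tied to having recorded sessions, they ask about barriers to using CPT, and they receive a full five-stage qualitative analysis. Clinicians who never deliver CPT can be heard there. This stands, and it confines the point to the quantitative analysis. Interviews can describe barriers, but they do not estimate the association that Hypothesis 3 asserts.
- The fidelity sentence is a mixed-methods integration step, meant for validation, hypothesis generation and expansion. It is not presented as the formal test of Hypothesis 3. This also stands. Even so, it is the only place where a quantitative outcome is named beside the contextual surveys.
- The plural outcomes of interest could include monthly activity. That is possible, but the article does not say so.
- Uptake may mean uptake of skill. Question 3 and the heading of the barriers section, which speaks of skills uptake, allow this. Fidelity would then be a fitting outcome, although still conditional on delivery and recording. That the text allows both readings is itself a reason to define the term.
- The article is condensed, so model details may sit elsewhere. Agreed, and no missing detail is criticised here. The point is that the outcome that is stated differs from the one in the hypothesis.
- Uploading was reported as high, so selection may be slight. This is fair, and any percentage bias quoted here depends on assumed inputs.

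**Conclusion.** The point holds in a limited form. As worded, Hypothesis 3 concerns uptake, and the one quantitative outcome named for the contextual surveys is fidelity among clinicians who delivered and uploaded CPT. That analysis alone cannot show whether context affects use of CPT. It can address Question 3's skilled use, conditional on delivery.

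The outcome mismatch rests on the text alone and would remain with complete uploading. Its numerical consequence cannot be derived from the document. The attenuation of 21% to 29% needs 20% of clinicians without a score and an engagement factor driving both delivery and fidelity. With 5% to 10% unscored it is about 10% to 20%. These figures show direction and scale and are not estimates for this trial. The aim is exploratory and the primary comparison is unaffected, so the change is worth making but does not threaten the trial.

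**What to change.** Under Research questions and hypotheses, define uptake as amount of CPT delivered. Under Proposed analytic strategy:

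- Name the monthly CPT session count and the new-client count as the quantitative outcomes of Hypothesis 3, in all randomised clinicians. Use a count model with a random clinician effect and arm as a covariate. The new-client figure is collected as a cumulative total, so use increments between reports or the last total, not the repeated totals as if they were separate counts.
- Keep reported zeros. Treat an unreturned report as missing, not as zero, and report how many were returned by arm.
- Keep the context-fidelity analysis as the answer to skilled use. Label it as conditional on having delivered and recorded CPT, and state how many clinicians in each arm have no fidelity score.

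If the sponsor meant uptake of skill, the lesser change is to reword Hypothesis 3 to fidelity. It would then make no claim about use.

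The cost is one extra model on data already collected, plus wording in two sections. The downside is that the counts are self-reported and disengaged clinicians may under-report or not reply, so the change reduces the selection problem without removing it.

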## Methods

This randomized controlled dismantling trial has independent fidelity rating as the primary outcome and patient outcomes as the secondary outcomes. Clinicians are randomly assigned to six months of post-workshop support following an intensive two-day CPT workshop delivered by the last author. The conditions are: standard group tele-consultation, technology-enhanced group tele-consultation, or no consultation/fidelity monitoring only. The post-workshop consultation conditions vary as to whether audio-recorded therapy sessions and other work samples, such as CPT worksheets, are reviewed in the group. This design permits the evaluation of the additive value of each of the elements (*i.e*., expert consultation, technology-assisted expert consultation). Follow-up assessments of fidelity will be conducted at six months post-workshop for clinicians, and follow-up symptom assessments will be conducted at three months post-treatment for patients.

Participation in the study requires that all clinicians consent at least two clients to have all of their CPT sessions audio-recorded for use in consultation and/or fidelity rating. Four therapy sessions will be randomly selected across the six-month period for fidelity rating, and fidelity to treatment will be assessed by trained graduate students and post-doctoral fidelity assessors. Consistent with recommended clinical practice and research trials, patient outcomes will be assessed pre-treatment, at alternate therapy sessions, and at three months post-treatment. A secure web-based application is used to manage the continuous uploading of encrypted audio-recorded therapy sessions to the study server and to protect the privacy and confidentiality of patients and clinicians. Study-provided digital audio-recorders (USB-equipped) are used to record, store and upload CPT sessions to the secure server for fidelity ratings. Study staff retrieve the randomly-selected audio-recordings and assign them to the CPT fidelity raters, who are blinded to study condition. To check if rater blinding has been achieved, fidelity raters will be asked to guess the study condition for each session they rated. Patient self-report data is collected by the clinicians, who then upload the data directly to the server and clinician CPT activity outside of study-related procedures is also recorded.

